### 2.3. Randomization and Blinding

After the baseline assessments, the physiotherapist that applied the interventions randomly allocated the participants to one of the intervention groups: the GPR group or the STE group. The randomization was undertaken by an independent assessor, with no other involvement in the trial, using a computerized randomization system (randomized.com; accessed date: 1 June 2020), and allocation concealment was guaranteed by sequentially numbered, opaque, sealed envelopes. Due to the nature of the intervention itself, the participating subjects were not blinded to the intervention, however, they did not know what type of exercise they received, having been informed only that they will receive an effective exercise treatment. To minimize contamination between groups, the assessors performing the study measurements of all outcome variables and the statistical analysis were blinded. The assessors did not know the group to which the subjects belonged in each of the evaluations, and the statistician performed the statistical analysis once all the variables were coded.

### 2.4. Procedures

Following the parameters of usual clinical practice and considering previous studies of GPR, according to some systematic reviews [55,92], and the protocols of STE in neck pain [54,93,94], the interventions were provided in eight sessions over a 4-week intervention period (two visits per week) accompanied by an individual daily at-home exercise program [64]. Baseline and follow-up assessments were conducted at the Polytechnic Institute of Guarda. There were four assessment points, and the time factor was considered in the statistical analysis with four levels. Initially, a test–retest reliability analysis was conducted on all participants to verify the variability between days. To achieve this, we applied two pre-intervention assessments, 1 week apart. After the second pre-intervention assessment, participants started the interventions in each group, and they will be assessed again in an intermediate evaluation after 2 weeks and four sessions of treatment (assessing only neck pain intensity, CROM, and cervical PPT outcomes) and in one last evaluation at the end of the intervention, 4 weeks and eight sessions of treatment (assessing all outcomes, such as in pre-intervention assessments). All data collected were confidential and private, ensuring anonymity of respondents. The participants were advised not to use other forms of treatment during the trial (pharmacologic or non-pharmacologic treatment). See the flow chart in Figure 1.

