### 2.6. Outcome Variables

In the first pre-intervention assessment, all variables were measured, including the sociodemographic variables. Later, all outcome variables were measured in the second pre-intervention assessment (baseline outcomes) and in the final assessment after the completed interventions (eight sessions in each group) (Table 6). As indicated above, in the intermediate evaluation (after four sessions of treatment) only the neck pain intensity, CROM, and PPT outcomes will be assessed (Figure 1).

Personal and sociodemographic variables:Age (years);Sex (male or female);Weight (kg); Height (m); Body mass index (kg/m^2^);Time feeling neck pain (years, months and weeks);Education level (no studies, basic education, secondary school, or superior studies);Marital status (single, married, separated, divorced, or widowed);Employment status.

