#### 2.6.1. Primary Outcome Variables

The primary measured outcomes of the study will be the change within groups and the differences between groups of the neck pain intensity and the neck disability at the assessment times.

Neck pain intensity

Neck pain intensity will be measured using a numerical pain rating scale (NPRS). This is an 11-point scale ranging from 0, which represents one pain extreme (e.g., “no pain”), to 10, which represents the other pain extreme (e.g., “pain as bad as you can imagine” and “worst pain imaginable”) [95]. The subject is instructed to select the number that best represents the mean of their pain in the last week. Evidence suggests that the perception of pain intensity in subjects with chronic pain must be analyzed by NPRS, and it has been demonstrated to be a valid and reliable scale [96,97]. NPRS has a high test–retest reliability and responsiveness when applied intra-observer reliability of (r = 0.76) in patients with mechanical neck pain [97] and in both literate and illiterate patients with rheumatoid arthritis (r = 0.96 and 0.95) [98]. NPRS also has a high validity with visual analogue scale (VAS) in patients with rheumatic and other chronic pain conditions (pain > 6 months) (correlations range from 0.86 to 0.95) [95], and a high convergent validity with VAS and verbal rating scale (VRS) (r = 0.82–0.92) [99]. Chronic pain patients prefer the NPRS over other measures of pain intensity due to its comprehensibility and ease of completion [99,100].

Neck Disability

We will measure the neck disability associated with pain using the Portuguese version of the neck disability index (NDI–PT), which is valid and reliable with excellent internal consistency (Cronbach’s alpha = 0.95). NDI–PT has a high test–retest reliability with an ICC = 0.91 [101,102], and NDI also has a highly convergent validity with a variety of pain scales (r = 0.40–0.71) [101]. NDI–PT is a patient-completed, condition-specific functional status questionnaire with 10 items including pain, personal care, lifting, reading, headaches, concentration, work, driving, sleeping, and recreation. Each section is rated on a scale of 0 to 5, where 0 means “painless” and 5 means “worst pain imaginable.” The points obtained are added to a total score between 0 and 50. The NDI-PT scores are presented as a percentage of the maximum score, 0–8% without disability; 10–28% mild; 30–48% moderate; 50–64% serious, and 70–100% complete disability [103,104].

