### 2.8. Statistical Analysis

Data were analyzed by using the IBM-SPSS software package (version 23.0). Descriptive data analysis was reported by groups as means ± standard deviation for numeric variables and as frequencies and percentages for categorical variables. In the graphical representation, bar graphs by groups were used for numeric variables, and pie charts were used to represent categorical variables. The main change from baseline to 4 weeks of treatment will be calculated using an intention-to-treat analysis for each outcome measure.

Two-way repeated measures ANOVA were performed. Group factors, as age range, were considered as categorical variables in the statistical model, such as potential covariates, and the Time factor will be used to take into account the two pre-intervention (baseline) and the intermediate and final data in the intervention (2 and 4 weeks of treatment). The interaction between the two factors on the dependent variables was analyzed. When the interaction was statically significant, follow-up tests (post-hoc Sidak test) were performed to determine how the within-participant factors affected the dependent variables, and it could be used as a covariate in the model. The post-hoc Sidak test was calculated to determine which pairs of means have significant differences.

Correlations with Pearson’s r coefficient were determined to analyze whether the values of two or more numeric variables change in conjunction or are related at some time point of the study.

The level of significance for the statistical tests were set at *p* ≤ 0.05 with a confidence interval of 95%.

In order to focus on clinical relevance or clinically worthwhile effects, and assess the magnitude of the change in the result variables, the effect size of both treatments for the group × time repeated-measures ANOVA model were calculated as the partial eta squared (ŋp^2^) when significant, considering 0.01 small, 0.06 medium, and more than 0.14 large effect sizes, and we could use the Cohen d for any pairwise comparisons, when applicable.

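### The four-level Time factor does not fit neck disability or four of the six secondary measures, which have only three time points

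*Protocol article*

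**What the plan says.** Section 2.4 describes two pre-treatment assessments a week apart, one after four sessions (2 weeks) and one after eight sessions (4 weeks). It states that "the time factor was considered in the statistical analysis with four levels".

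Section 2.8 specifies a two-way repeated-measures ANOVA in which "the Time factor will be used to take into account the two pre-intervention (baseline) and the intermediate and final data in the intervention". No outcome is exempted. If the interaction is significant, Sidak follow-up tests are run. Partial eta squared for the group-by-time model is also tied to significance. The same section names the change from baseline to 4 weeks, by intention to treat, as the main change for each outcome.

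The visit schedule differs by outcome. Section 2.4 describes the 2-week visit as "assessing only neck pain intensity, CROM, and cervical PPT outcomes". Section 2.6 repeats that "only the neck pain intensity, CROM, and PPT outcomes will be assessed" there.

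Section 2.6.1 defines the primary outcomes as "the change within groups and the differences between groups of the neck pain intensity and the neck disability at the assessment times". It does not say that the two outcomes have different assessment times.

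**The concern.** The article prescribes a Time factor that its own schedule cannot supply for one of its two primary outcomes. This is a stated rule that conflicts with a stated schedule, so it is not a detail left to a fuller plan.

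The number of levels has consequences. The interaction test decides whether pairwise comparisons follow, and the number of levels sets both its degrees of freedom and the size of the Sidak family. Someone analysing NDI must depart from the text. Two departures can be defended from the article: three levels (every visit at which NDI is measured), or two levels (second pre-treatment visit and 4 weeks, since section 2.5 calls the second evaluation the baseline). The article does not say which.

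**Working it through.** **1. The plan's own figure.** Two pre-treatment + one intermediate + one final assessment = 4. The figure is right as a count of visits.

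**2. Levels measured per outcome** (sections 2.4 and 2.6; roles from sections 2.6.1, 2.6.2 and Table 6).

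| Outcome | Role | Pre-1 | Pre-2 | 2 wk | 4 wk | Levels |
|---|---|---|---|---|---|---|
| NPRS | primary | yes | yes | yes | yes | 4 |
| NDI | primary | yes | yes | no | yes | 3 |
| CROM | secondary | yes | yes | yes | yes | 4 |
| PPT | secondary | yes | yes | yes | yes | 4 |
| COP | secondary | yes | yes | no | yes | 3 |
| EMG | secondary | yes | yes | no | yes | 3 |
| TSK | secondary | yes | yes | no | yes | 3 |
| PCS | secondary | yes | yes | no | yes | 3 |

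Affected: 1 of 2 primary outcomes and 4 of 6 secondary measures. Table 6 groups TSK and PCS under attitude to pain, so by domain it is 3 of 5.

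**3. Can the four-level model be fitted to NDI?** Two groups × 4 times = 8 cell means. Data exist in 2 × 3 = 6 cells, so the design matrix has rank 6 and the two 2-week cells are not estimable. With three levels there are 6 cells and rank 6, so that model can be fitted. The 2-week values are absent by design in all 62 participants, so neither imputation nor a mixed model can recover a 2-week effect from the NDI data.

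**4. What changes with the number of levels.** With g = 2 groups, k levels and N participants, the interaction has (g − 1)(k − 1) df and its error term (N − g)(k − 1) df. If the Sidak family is all k(k − 1)/2 pairs of times within an outcome (an assumption, as the article does not define it), the per-pair level is 1 − 0.95^(1/pairs). With N = 52, the evaluable number in section 2.2:

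| Levels | Interaction df | Error df | Time pairs | Per-pair alpha |
|---|---|---|---|---|
| 4 (NPRS) | 3 | 50 × 3 = 150 | 6 | 0.0085 |
| 3 (NDI, all its visits) | 2 | 50 × 2 = 100 | 3 | 0.0170 |
| 2 (baseline and 4 weeks) | 1 | 50 × 1 = 50 | 1 | 0.05 |

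With all 62 participants the error df are 180, 120 and 60. The other columns do not change.

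**5. Sample size.** A two-sample t-test with d = 0.8, two-sided alpha 0.05 and power 0.80 needs 25.52 per group, rounded up to 26. Then 52 / (1 − 0.15) = 61.2, rounded up to 62. Both figures match section 2.2, and neither calculation uses the number of time levels.

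**6. Main change.** NDI and every other outcome are measured at the second pre-treatment visit and at 4 weeks, so the change named in section 2.8 can be estimated throughout.

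**The case against.** The strongest reply is that the four-level phrase counts visits. It stands in the same paragraph as the 2-week restriction, so a sensible reader would analyse each outcome at the visits where it was measured. On that reading the NDI levels are fixed by the schedule, and the three-level model is fittable. Having more tests or degrees of freedom for an outcome measured once more is a legitimate result of the design. The reference in section 2.6.1 to the assessment times need not mean all four. This is also a condensed article, and listings by outcome often sit in a fuller plan.

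Much of this stands. Three levels is the likeliest repair, unequal df are not a fault in themselves, and section 2.6.1 is weak evidence of a conflict. But the phrase concerns the Time factor in the statistical analysis, not only the visits, and section 2.8 lists the same four data points for the ANOVA without exception. A likely repair is not a stated one, and the two-level alternative also has support in the text.

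A reader might go further and infer that no analysis exists for NDI, because 0 of 62 participants can have four NDI values. The documents do not support that. Section 2.8 names the change from baseline to 4 weeks as the main change, section 2.2 bases the sample size on change from baseline to the final assessment, and NDI is measured at both ends.

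**Conclusion.** The point holds as a mis-specified analysis. The four-level Time factor cannot be fitted to NDI, COP, EMG, TSK or PCS, and no section gives an alternative number of levels for them. If every measured visit is kept, NPRS is judged by a 3-df interaction with six time pairs and NDI by a 2-df interaction with three. The article prespecifies neither the NDI model nor the difference.

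The data are not compromised, the sample size is unaffected, and the 4-week comparison remains available for both primary outcomes. A reader might also infer that the two primary outcomes would answer different questions. That goes too far: both would be tested by a group-by-time interaction of the same type, and the contrast from the second pre-treatment visit to 4 weeks is common to both.

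The conclusion rests on the 2-week visit having been run as sections 2.4 and 2.6 describe. The Sidak figures rest on the assumed family, and the error df on complete data.

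**What to change.** In sections 2.4 and 2.8, replace the single four-level statement with levels by outcome: four for NPRS, CROM and PPT (pre-1, pre-2, 2 weeks, 4 weeks), and three for NDI, COP, EMG, TSK and PCS (pre-1, pre-2, 4 weeks). In section 2.6.1, say which assessment times apply to each primary outcome.

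That removes the contradiction. To put both primary outcomes on the same footing, also name one common primary test for NPRS and NDI: the between-group difference at 4 weeks, adjusted for the second pre-treatment value, which sections 2.5 and 2.6 treat as baseline. This goes a step beyond the minimum repair, but it matches the baseline-to-final basis of sections 2.2 and 2.8. The 2-week visit is then a secondary time point, for NPRS, CROM and PPT only.

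The cost is wording, with no new data or visits. What is given up is that the week-2 NPRS profile moves from the primary to a secondary analysis. The change should be made before the groups are compared. The article mixes past and future tense on the analysis, so it does not show whether that has already happened.

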### 2.5. Interventions

The interventions were conducted by an experienced physiotherapist with more than 7 years in the treatment of the musculoskeletal disorders with these interventions.

The interventions in both groups commenced after the second evaluation, which we considered the baseline assessment. The interventions in both groups were performed for 4 weeks, and they consisted of a combination of treatment sessions carried out by a physiotherapist and exercises to be performed at home. The physiotherapist performed two sessions per week [64] with the participants in each group, and participants were asked to practice their prescribed exercise program at home, depending the group, once daily for 4 weeks, and to complete an exercise diary to monitor compliance and record adverse events. Each session of treatment lasted approximately 35 min for the STE group and 45 min for the GPR group, according to clinical practice and previous studies [54,55,92,93,94]. The physical therapist taught and showed a detailed home exercise program for all participants, where the physiotherapist provided easy and simple home exercises without devices. Participants in GPR group performed at home one lying posture and the STE group prescribed active movements and stretches of the neck muscles (Table 2).

Participants assigned to the GPR group performed global postural exercises consisting of three positions, following the protocol of Lozano-Quijada C. et al. [82] (Figure 2). Initially, without gravity load, a lying posture was applied to the anterior muscle chain for approximately 15 min, then another lying posture to the posterior muscle chain for other 15 min, and finally the patients worked in a standing posture for postural integration under a gravity load for 5 min. Between each posture there was a short resting time.

Participants assigned to the STE group performed specific therapeutic exercises for motor control, divided into three phases, following the protocol of Jull G. et al. [54,93] and Sremakaew M. et al. [94]. Each of the phases had two exercises with visual feedback with a laser sensor (motion guidance: a laser pointer rehab tool that adds visual feedback for motor control during exercise in physical therapy) (Figure 3).

In both interventions, all exercises were performed following a progression in intensity. The physiotherapist tried to ensure that the patients performed all the exercises as correctly as possible with the appropriate and expected intensity, although it was necessary to be careful and always consider possible exercise adaptations to respect the individuality, as a principle of GPR, of each subject (such duration of the pause between exercises, changes in manual contacts, time applied to each posture, or type of breathing of GPR).

The exercise programs for both interventions are described in Table 3. In addition, details of the exercise progression for each group are presented in Table 4 and Table 5.

In GPR the process of progression will depend a lot on the individuality of each participant. This means that we increased the stretch while the participant was able to maintain all postural corrections without compensation.

### 2.6. Outcome Variables

In the first pre-intervention assessment, all variables were measured, including the sociodemographic variables. Later, all outcome variables were measured in the second pre-intervention assessment (baseline outcomes) and in the final assessment after the completed interventions (eight sessions in each group) (Table 6). As indicated above, in the intermediate evaluation (after four sessions of treatment) only the neck pain intensity, CROM, and PPT outcomes will be assessed (Figure 1).

Personal and sociodemographic variables:Age (years);Sex (male or female);Weight (kg); Height (m); Body mass index (kg/m^2^);Time feeling neck pain (years, months and weeks);Education level (no studies, basic education, secondary school, or superior studies);Marital status (single, married, separated, divorced, or widowed);Employment status.

#### 2.6.1. Primary Outcome Variables

The primary measured outcomes of the study will be the change within groups and the differences between groups of the neck pain intensity and the neck disability at the assessment times.

Neck pain intensity

Neck pain intensity will be measured using a numerical pain rating scale (NPRS). This is an 11-point scale ranging from 0, which represents one pain extreme (e.g., “no pain”), to 10, which represents the other pain extreme (e.g., “pain as bad as you can imagine” and “worst pain imaginable”) [95]. The subject is instructed to select the number that best represents the mean of their pain in the last week. Evidence suggests that the perception of pain intensity in subjects with chronic pain must be analyzed by NPRS, and it has been demonstrated to be a valid and reliable scale [96,97]. NPRS has a high test–retest reliability and responsiveness when applied intra-observer reliability of (r = 0.76) in patients with mechanical neck pain [97] and in both literate and illiterate patients with rheumatoid arthritis (r = 0.96 and 0.95) [98]. NPRS also has a high validity with visual analogue scale (VAS) in patients with rheumatic and other chronic pain conditions (pain > 6 months) (correlations range from 0.86 to 0.95) [95], and a high convergent validity with VAS and verbal rating scale (VRS) (r = 0.82–0.92) [99]. Chronic pain patients prefer the NPRS over other measures of pain intensity due to its comprehensibility and ease of completion [99,100].

Neck Disability

We will measure the neck disability associated with pain using the Portuguese version of the neck disability index (NDI–PT), which is valid and reliable with excellent internal consistency (Cronbach’s alpha = 0.95). NDI–PT has a high test–retest reliability with an ICC = 0.91 [101,102], and NDI also has a highly convergent validity with a variety of pain scales (r = 0.40–0.71) [101]. NDI–PT is a patient-completed, condition-specific functional status questionnaire with 10 items including pain, personal care, lifting, reading, headaches, concentration, work, driving, sleeping, and recreation. Each section is rated on a scale of 0 to 5, where 0 means “painless” and 5 means “worst pain imaginable.” The points obtained are added to a total score between 0 and 50. The NDI-PT scores are presented as a percentage of the maximum score, 0–8% without disability; 10–28% mild; 30–48% moderate; 50–64% serious, and 70–100% complete disability [103,104].

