We considered the conclusions and indications of previous studies, based on the need for high-quality prospective clinical trials comparing GPR with effective treatment strategies for neck pain, such as manual therapy or therapeutic exercises [15,55,56,59]. Taking into account what has been described above, we considered it interesting to contribute more knowledge regarding the use in clinical practice of a wider variety of methods based on exercise and manual therapy. In our study we address the GPR, which due to the heterogeneity of the results of some studies, it presents some lack of evidence that we address in our study, on parameters in the application protocols and the effects on some outcome variables not sufficiently assessed in previous studies as patterns or neuromuscular efficiency, postural control and psychosocial factors, and also compare these effects with those caused by other therapies in this study factor (CNSNP).

Therefore, this randomized parallel clinical trial will aim to evaluate the benefits of GPR and STE, as two different exercise modalities, the former more dynamic [46,47,49,54], and the latter more static/postural [61,73,77], considering that both have mechanisms of action targeting symptomatology [46,47,55,56] and muscle efficiency [46,54,68]. So, pain, disability, postural control, neuromuscular function, and the correlations between them will be assessed in women with chronic non-specific cervical pain. The primary objective is to investigate the most effective and efficient intervention to improve neck pain intensity and disability. More concretely, we will evaluate if a global postural exercise method, such as GPR, or a specific therapeutic exercise has a superior effect. The secondary objective is to assess the effectiveness of the two interventions on cervical range of motion (CROM), pressure pain threshold (PPT) in the cervical region, kinesiophobia, pain catastrophizing, standing postural control, and neuromuscular efficiency of superficial cervical flexor muscles.

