### 2.2. Participants, Recruitment and Sample Size Calculation

A sample of 62 women with CNSNP were recruited between 30 and 65 years old from the community in Guarda, Portugal. Participants were recruited through an online google form, with a questionnaire in Google Docs format, which was disseminated through social network postings (Facebook and Instagram) and the sending of institutional emails from Polytechnic Institute of Guarda to its workers. There were two physiotherapist assessors, who initially assessed participants that responded to the advertisements, and they were different from the physiotherapists who performed the interventions in both groups. In the first visit, the participants provided oral and written forms of all necessary information about the trial, including the study purpose and procedure. After voluntarily signing the informed consent statement, if through a detailed interview they met all inclusion, exclusion, and withdrawal criteria (Table 1), they enrolled into the trial to begin with an initial evaluation with the assessors.

The sample size calculation has been made based on the potential modification of the primary outcomes, neck pain intensity, and neck disability (NPRS and the NDI-PT) from baseline to final assessments. For repeated measurements of the estimated sample size, accepting an alpha risk of 0.05 and a beta risk of 0.2 in a two-sided test, 26 subjects were necessary in the first group and 26 in the second to recognize a statistically significant difference greater than or equal to 2 units (SD = 1.75) (NPRS) or 7 units (SD = 6) (NDI), and to detect small differences in standardized means between groups (Cohen’s d = 0.8), since the intervention with therapeutic exercise is known to have a beneficial effect and we want to assess whether the intervention with GPR has similar or even greater effects. Finally, considering a 15% loss rate during the study, and in order to end up with a sample of 52 subjects, based on the power analysis results, the final sample to be recruited was 62 subjects, 31 in each group. The sample size calculation was made with the software “PASS 15 (NCSS statistical software)” and “The R Project for Statistical Computing”.

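### Within-group change is named as a primary outcome beside the between-group difference, unranked, although the trial's question and its sample size are both comparative

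*Protocol article*

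**What the plan says.** The Introduction sets a comparative primary objective: "we will evaluate if a global postural exercise method, such as GPR, or a specific therapeutic exercise has a superior effect".

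Section 2.6.1 then states that the primary outcomes "will be the change within groups and the differences between groups of the neck pain intensity and the neck disability", at the assessment times. It gives no order between the two parts and no rule for which one answers the objective. Section 2.6.2 uses the same formula for the secondary outcomes.

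Section 2.8 contains four relevant statements:
- On change: "The main change from baseline to 4 weeks of treatment will be calculated using an intention-to-treat analysis for each outcome measure". No contrast between groups is named.
- On the two-way repeated measures ANOVA: "The interaction between the two factors on the dependent variables was analyzed".
- On follow-up: "When the interaction was statically significant, follow-up tests (post-hoc Sidak test) were performed to determine how the within-participant factors affected the dependent variables".
- Again on follow-up: "The post-hoc Sidak test was calculated to determine which pairs of means have significant differences". This sentence states no condition and does not say which pairs.

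Section 2.2 bases the sample size on both raw units (NPRS 2, SD 1.75; NDI 7, SD 6) and a between-group d of 0.8, "accepting an alpha risk of 0.05 and a beta risk of 0.2 in a two-sided test".

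**The concern.** Randomisation protects the comparison between arms. It does not protect the change from before to after treatment within one arm.

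Both arms here receive exercise treatment and there is no untreated arm. Women enter with neck pain lasting more than 12 weeks and an NPRS of at least 2 (Table 1). Section 2.2 itself expects therapeutic exercise to help. Improvement within each arm is therefore likely in advance, and it combines any treatment effect with natural course, regression to the mean and expectation.

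Such a change cannot tell the reader whether GPR or STE is better, yet it has the same primary standing as the comparison that can. At stake is a report that presents improvement in both arms, or in one of them, as a primary result when the treatments do not differ.

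**Working it through.** **1. What the stated sample size rests on.** Inputs from section 2.2: two-sided alpha 0.05, power 0.80, 15% loss. Per group, n = 2(1.960 + 0.842)² / d².

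| Input | d | n, normal approximation | n, two-sample t |
|---|---|---|---|
| Stated d | 0.8 | 24.5, so 25 | 25.5, so 26 |
| NPRS 2 / 1.75 | 1.143 | 12.02, so 13 | 13.05, so 14 |
| NDI 7 / 6 | 1.167 | 11.5, so 12 | 12.6, so 13 |

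The stated 26 is reproduced by d = 0.8 with the t-test, and 52 / 0.85 = 61.2, so 62. Neither raw pair gives 26. The trial is sized for a between-group effect.

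**2. Within-arm tests when the arms are equal.** Suppose both arms improve by the same amount, so the true group difference is zero. Inputs: n = 26 per arm and SD 1.75 (section 2.2). Assumptions:
- 1.75 is the SD at a single visit. The article does not say whether it is that or the SD of change.
- The baseline-final correlation r lies between 0 and 0.76. The upper end borrows the NPRS reliability coefficient quoted in section 2.6.1.
- Each arm has a paired t-test at 0.05, unadjusted.

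SD of change = 1.75 × √(2(1 − r)). With p the per-arm power, P(at least one arm) = 1 − (1 − p)² and P(both arms) = p².

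| r | SD of change | 1 point: one given arm | at least one | both | 2 points: one given arm | at least one | both |
|---|---|---|---|---|---|---|---|
| 0 | 2.47 | 0.508 | 0.758 | 0.26 | 0.977 | 0.9995 | 0.955 |
| 0.4 | 1.92 | 0.725 | 0.924 | 0.53 | 0.999 | >0.999 | 0.998 |
| 0.6 | 1.57 | 0.879 | 0.985 | 0.77 | >0.999 | >0.999 | >0.999 |
| 0.76 | 1.21 | 0.981 | >0.999 | 0.96 | >0.999 | >0.999 | >0.999 |

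At 1.5 points, the per-arm probability runs from 0.844 to nearly 1.

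At r = 0.5 the single-visit SD and the SD of change are both 1.75, so the two readings of that figure coincide. There, at least one arm is significant with probability 0.49, 0.96 and >0.999 for shared improvements of 0.5, 1 and 2 points. With a Sidak correction over six time pairs (assumed; per-test level 1 − 0.95^(1/6) = 0.0085) these become 0.19, 0.78 and about 1.

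**3. The route through the interaction.** A simulation used 20,000 runs per setting, 26 per arm, four time points, SD 1.75, correlation 0.5 and equal arms, with shared improvements of 0.5 to 2 points. The group × time interaction was significant in 4.9% to 5.2% of runs. A significant Sidak-adjusted within-arm change after a significant interaction occurred in 2.2% to 5.0%. With 31 per arm the pattern is the same.

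**The case against.** The strongest reply is that the plan already tests the right thing. Section 2.8 analyses the group × time interaction, which compares the arms, and makes the first Sidak follow-up conditional on it. **This stands.** By that route, false positives stay at about 5% or less. A reader might infer that the within-participant follow-up tests inflate them; the stated condition rules that out for the first Sidak sentence.

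Second, nothing in the article says when the primary outcome counts as met. Section 2.6.1 joins the two parts with a plain conjunction, and if both were required, equal arms would pass about 5% of the time. **This also stands.** It rules out the tempting stronger reading that a positive primary result is almost certain in both arms. That reading also needs a shared improvement near 2 points: at 1 point, both arms are significant only 26% to 96% of the time over the assumed correlations.

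Third, a reader might infer that the trial will compare one arm's significance with the other arm's lack of it. No such rule appears in the article.

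Fourth, two pre-intervention assessments a week apart, with the second used as baseline (sections 2.4 and 2.5), reduce regression to the mean. They do so only in part, and do nothing about natural course or expectation during treatment.

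None of this removes the mismatch in section 2.6.1. Nor does section 2.8 resolve it: the first follow-up is aimed at time effects, the second Sidak sentence has neither condition nor pairs, and the sentence on change to 4 weeks names no group contrast. Naming the primary outcome is not a detail to leave to an analysis plan; the article states it, in a form that does not match the objective.

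**Conclusion.** The point holds in a limited form. Section 2.6.1 gives within-group change the same primary standing as the between-group difference, while the objective and the basis of the sample size are comparative. Within-group change cannot answer which modality is superior.

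The numerical consequence is conditional. Only if within-group change were taken as a criterion of primary success would equal arms give a positive result in at least one arm with probability 0.76 to 1.00 (1 point) or above 0.99 (2 points), against about 5% for the interaction test. The within-arm figures rest on 26 per arm, unadjusted tests, 1.75 as a single-visit SD and correlations of 0 to 0.76. Sidak adjustment or a smaller shared improvement lowers them, but at r = 0.5 even a half-point improvement with Sidak over six pairs gives 0.19.

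The wording should be corrected. The planned interaction test is not itself at fault.

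**What to change.** - **Section 2.6.1:** define the primary outcome as the between-group difference (GPR minus STE) in NPRS and in NDI at 4 weeks, adjusted for the score at the second pre-intervention assessment. The adjustment is a recommended method; the essential step is to make the group contrast primary.
- **Sections 2.6.1 and 2.6.2:** report within-group change descriptively, as mean change with 95% CI and no claim of efficacy, for primary and secondary outcomes alike.
- **Section 2.8:** direct follow-up tests to group differences at 4 weeks, and at 2 weeks only for outcomes measured then (pain intensity, CROM and PPT, so not NDI). State the pairs and the condition for the second Sidak sentence, or merge it with the first.

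The cost is wording. No data or patients are affected, and the sample size stays at 62 because it already rests on a between-group effect. Section 2.2 reports recruitment as complete, so the change to the primary outcome should be dated and documented as made before unblinded analysis.
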